## 11. STUDY DESIGN AND STATISTICS

### 11.1 Study design

GEIS-51 is a multicenter, open-label, non-randomized, phase II clinical trial that initially had a single cohort of advanced sarcomas with CDK4 overexpression. Subsequently, a second phase (additional cohort) focused only on chordomas has been included. The study will be conducted only in Spain including the participation of third level hospitals.

### 11.2 Analytical variables

#### **Main endpoint**

- Efficacy measured by progression free survival (PFS) rate at 6 months, evaluated using RECIST 1.1. criteria.

#### **Secondary endpoints**

- Efficacy measured by overall response rate (ORR) (complete response [CR] and partial response [PR]), evaluated with RECIST 1.1. criteria. The evaluation criteria will be based on the identification of target lesions at baseline and their follow-up until tumor progression.
- Efficacy measured by response according to Choi criteria. The evaluation criteria will be based on the identification of target lesions at baseline and their follow-up until tumor progression.
- Efficacy measured by median PFS.
- Efficacy measured by PFS rate at 3 months.
- Overall survival (OS) measured from the date of initiation of treatment with palbociclib until the date of death, regardless of cause.
- Clinical benefit rate (CBR). Patients who have shown complete response, partial response or disease stabilization for 6 months or more, showing signs of clinical improvement, will be considered to have experienced clinical benefit.
- Safety profile of palbociclib, by evaluation of adverse events (type, incidence, severity, time of occurrence, related causes) observed on physical examinations and laboratory tests. Toxicity will be analyzed and tabulated using NCI-CTCAE 4.0 (first phase; STS and BS) and 5.0 (second phase; chordomas).

### 11.3 Sample size and statistical plan

#### *Sample size – First phase (STS and BS)*

According to the initial design for the first phase of STS and BS (Simon's two-stage), for an alpha error of 0.1 and a power (beta error) of 0.90, H0 14% (cut-off for active drugs, progression free survival rate at 6 months according to EORTC experience) and H1 35% of progression free survival rate at 6 months were estimated. In the first stage, 15 patients had to be recruited, of whom at least 3 had to have a progression free survival greater than 6 months. If this occurred, then a second stage would continue with further 23 treated patients, until reaching a total of 38 evaluable patients. If at least 9 patients had 6-month PFS or longer, further investigation of the drug would be warranted.

The design of the first phase has been amended preserving, to the extent possible, the differences between H0 and H1, due to low recruitment. The new approach is a Simon's two-stage Minimax design (type 1 and type 2 errors at 10%), H0 15% and H1 40%. If 2 or fewer successes are observed in the first 15 patients recruited, the trial will be stopped in this cohort with the conclusion that the investigational drug should not be further investigated in this subgroup of patients. In another case (3 or more successes in the first 15 patients recruited, PFS greater than 6 months) patient recruitment will continue up to 21 evaluable patients. If 6 or more successes are observed in these 21 patients, it will be concluded that the results of this trial deserve further investigation.

#### *Sample size – Second phase (chordomas)*

For the chordoma cohort (second phase), the primary variable of analysis is the rate of patients with PFS greater than 6 months. Since the mechanism of action is based on a reduction of viability in relation to G1 tumor cell arrest rather than apoptosis, it seems more reasonable to maintain this primary endpoint.

The first prospective study in chordoma with a systemic drug (9-nitro-camptothecin) showed a 33% PFS rate at 6 months. Stacchiotti reported a 6-month PFS rate of 65% while Schueltze obtained, with dasatinib, a 54% PFS rate at 6 months.

A Simon's two-stage Minimax design is considered, with type 1 and 2 errors of 10%. Success at 30% or less will be considered unacceptable and would not require further investigation (null hypothesis). Thus, the value of H0 will be 30%. Success in 60% of cases or more will be considered an acceptable result (H1, alternative hypothesis, 60%).

A total of 9 eligible and treated patients will be included in the first stage of this cohort. If 2 or fewer successes are seen, then the trial will be stopped in this cohort with the conclusion that the investigational drug should not be investigated further in chordoma. Otherwise (3 successes or more), recruitment will continue until 19 evaluable patients have entered the study. If 9 or more patients are successful among these 19 patients, it will be concluded that the results of this trial deserve further investigation.

### *Analytical methodology*

For variables that follow binomial distributions (e.g., response rate), frequencies and percentages will be calculated, along with their exact (95%) confidence intervals. For time-to-event variables (e.g., PFS or OS), Kaplan-Meier estimates will be used. To analyze risk reduction and the influence of other variables on time-to-event variables, Cox Regression will be used. To correlate pharmacodynamic markers and biomarkers with clinical response, standard methods for bivariate and multivariate regression and correlation will be used. Multivariable methods will only be used if the required assumptions are verified.

#### 11.4 Efficacy analysis

The populations for efficacy evaluations will be as follows:

- Intention-to-treat (ITT) population: Patients who signed the informed consent, having a central diagnosis and molecular expression confirmation, fulfilling all the inclusion criteria and none of the exclusion criteria.
- Per-protocol (PP) population: An efficacy analysis will be conducted in the PP population, which is defined as the subset of ITT population, without significant protocol deviations, with measurable disease (according to RECIST 1.1) at baseline, having had at least one cycle of study treatment and one radiological re-evaluation.

#### 11.5 Safety analysis

Any patient included in the study who has received at least one dose of the investigational medication will be evaluable for the toxicity analysis. The safety profile will be characterized by adverse events related to study medication, vital signs, and laboratory test abnormalities. The evaluation of adverse events will include the type of event, severity (according to National Cancer Institute [NCI] Common Terminology Criteria for Adverse Events [CTCAE] grades, version 4.0 for the first phase –STS and bone sarcomas– and 5.0 for the second phase – chordomas), onset and end dates, the relationship and action taken with the study medication, other measures taken, and the outcome of the event. Tumor-related signs and symptoms observable in the pre-treatment (baseline) period will be recorded as adverse events during the trial if they worsen in severity or increase in frequency. In all visits, all adverse events will be recorded following the NCI-CTC version 4.0 terminology for the first phase (STS and bone sarcomas) and 5.0 for the second phase (chordomas).

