**Table 3: Laboratory tests**

## 7.6 Safety evaluations

Any patient enrolled in the study who has received at least one dose of the trial medication will be evaluable for toxicity analysis. The safety profile will be characterized by treatment-emergent adverse events, vital signs, and laboratory abnormalities. Evaluation of adverse events will include type of event, incidence, severity (measured according to NCI-CTCAE 4.0 in the first phase of STS and bone sarcomas, and 5.0 in the second phase of chordomas), timing, and relationship to trial medication. Tumor-related signs and symptoms at baseline will be recorded as adverse events during the trial if they worsen in severity or increase in frequency. All adverse events will be recorded at each study visit.

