**AE registration**

The Sponsor (through the assigned CRO in charge of pharmacovigilance) will collect the AEs up to 30 days after administering the last dose of the study drug. All adverse events will be recorded using medical terminology in the source document and in the electronic CRF. Investigators should assess the severity (grade) of the event using the NCI-CTCAE 4.0 (first phase; STS and bone sarcomas) and 5.0 (second phase; chordomas) criteria, assigning a possible relationship to the study drug and obtaining adequate information to determine the outcome and assess whether it is a serious adverse event requiring immediate reporting. The investigator should provide any information requested by the Sponsor in addition to that contained in the CRFs.

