**SAE reporting**

Any serious adverse event (SAE) occurring from the moment the patient's informed consent is signed, during the clinical trial, and up to 30 days after receiving the last dose of the trial medication, whether drug-related or not, should be reported by the investigator. Moreover, any SAE occurring as a result of a protocol-specific process or intervention should also be reported. Beyond this time period, only those SAEs that are suspected to be related to the study drug shall be reported.

All SAEs suspected to be related to study treatment must be followed up after treatment/study withdrawal, until the event or its symptoms have been resolved or stabilized to a degree acceptable to the investigator and the Sponsor.

The local investigator team must notify the Sponsor (through the assigned CRO) of all female patient pregnancies occurring during the clinical trial within 24 hours of becoming aware of the event. The research staff of the center must also communicate the result of the pregnancy within 24 hours from the time they become aware of the situation.

The cause of death of a deceased clinical trial patient, whether it is an expected event or associated with the trial drug, is considered an SAE and, therefore, should be reported using the SAE form. The autopsy report must be sent to the Sponsor, indicating only the number of the patient in the trial.

Investigator teams must communicate by fax or email all SAEs and SUSARs within 24 hours to the trial CRO:

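### Section 11.5 limits the adverse event part of the safety profile to drug-related events, contradicting section 7.6 and the safety endpoint in section 11.2

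*Protocol*

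**What the plan says.** Section 11.5 (Safety analysis) states: "The safety profile will be characterized by adverse events related to study medication, vital signs, and laboratory test abnormalities". Section 7.6 (Safety evaluations) states: "The safety profile will be characterized by treatment-emergent adverse events, vital signs, and laboratory abnormalities". The safety endpoint in section 11.2, repeated in the Summary, reads: "Safety profile of palbociclib, by evaluation of adverse events (type, incidence, severity, time of occurrence, related causes) observed on physical examinations and laboratory tests".

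Later in 11.5, the items evaluated for adverse events include "the relationship and action taken with the study medication, other measures taken, and the outcome of the event". The section also has tumor-related signs and symptoms present at baseline recorded as adverse events if they worsen, and continues: "In all visits, all adverse events will be recorded following the NCI-CTC version 4.0 terminology" (version 5.0 for chordomas).

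Section 8.2 has the investigator grade each event, "assigning a possible relationship to the study drug and obtaining adequate information to determine the outcome". It collects adverse events until 30 days after the last dose. SAEs in the reporting period are covered "whether drug-related or not, should be reported by the investigator".

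**The concern.** Treatment-emergent is a matter of timing. Related is a matter of the investigator's causality judgement. The two sentences therefore name different sets of events for the same deliverable, and the narrower set stands under the heading that an analyst would turn to first. An analysis plan drafted from 11.5 alone could tabulate only attributed events and still comply with the protocol.

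The choice matters more here than in a controlled, blinded trial. Section 11.1 describes an open-label, non-randomized study, and each cohort has a single arm. Attribution is made with knowledge of treatment, and there is no comparator rate against which to judge it. A summary of all events would let the reader weigh attribution. A summary of related events alone would not.

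**Working it through.** No figure in the protocol depends on this point, so there is no stated number to reproduce. The check is a comparison of the passages.

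**Adverse event scope, place by place**

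| Place | Scope of adverse events | Role of causality |
|---|---|---|
| 7.6, profile sentence | Treatment-emergent | None in the scope; relationship is a listed attribute |
| 11.2 and Summary, safety endpoint | Adverse events, unrestricted | Attribute |
| 11.5, profile sentence | Related to the drug | Filter |
| 11.5, items evaluated | Adverse events | Attribute |
| 11.5, recording at visits | All adverse events | None |
| 8.2, AE registration | Adverse events to 30 days after last dose | Attribute, assigned by the investigator |
| 8.2, SAE reporting | SAEs to 30 days after last dose, related or not | None within that period |

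The profile sentence in 11.5 is the only entry that uses causality as a filter. It also fits poorly with the sentence after it: listing relationship among the items evaluated has little purpose if only related events are analysed.

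**What the literal reading removes**

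1. Let E be the treatment-emergent adverse events and R those within E that are judged related. The 7.6 sentence reports E; the 11.5 sentence reports R. The difference is the events in E judged unrelated.
2. If u is the share of E judged unrelated, the share of E reported under 11.5 is 1 − u. The protocol gives no adverse event rates and no value for u, so the effect cannot be sized.
3. The denominator does not change. In 7.6 as in 11.5, any enrolled patient who "has received at least one dose of the investigational medication will be evaluable for the toxicity analysis" (7.6 has equivalent wording). Only the numerator is in dispute.
4. For scale only, assuming that all planned patients are dosed: one patient counted or not counted moves an incidence by 1/21 = 4.8 percentage points in cohort 1 and 1/19 = 5.3 in cohort 2. This is the step size of the estimate, not an estimate of the effect.

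**A second difference in the same text**

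Sections 7.6 and 11.2 both list incidence among the features of adverse events to be evaluated. The list in 11.5 omits it.

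**The window**

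Section 7.6 uses the term treatment-emergent without giving a window. Section 8.2 gives the end of adverse event collection (30 days after the last dose) but no start, while SAE reporting starts at consent. The schedule in Table 2 shows adverse events across the treatment columns, but that is not a definition.

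**The case against.** The strongest reply is that 11.5 should be read as a whole and alongside 11.2. The protocol gives 11.5 no precedence over 11.2, which is in the same chapter and defines the endpoint without restriction. Section 11.5 itself treats relationship as an attribute and has all events recorded. On that reading, one phrase is loosely worded and the intended analysis is the wider one. This argument stands as evidence of intent, and it supports the direction of the correction. It does not remove the contradiction, because the narrower sentence remains in force and can be followed as written.

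A reader might infer that the analysis is bound to omit every event judged unrelated. The documents do not support that. Vital signs and laboratory abnormalities enter the profile with no causality filter, and other text in 11.5 and 11.2 points to the full set.

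A reader might also infer that safety signals, respiratory events in particular, would be hidden. That does not follow either. Surveillance for interstitial lung disease and pneumonitis in section 8.6 operates on individual patients. SAEs are reported whether or not they are related, and under section 8.4 the sponsor keeps a record of all reported adverse events and continuously evaluates benefit and risk. None of this depends on how the summary in 11.5 is built.

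The layout of tables may fairly be left to the statistical analysis plan, and its absence here is not the finding. The finding is that the protocol itself fixes the event set twice, and differently.

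**Conclusion.** The contradiction is certain on the wording. Section 11.5 restricts the adverse event component to related events; section 7.6 and the endpoint in 11.2 do not, and the remainder of 11.5 fits the unrestricted version. On the literal reading, events judged unrelated by an unblinded investigator would be missing from the adverse event summary, with no control arm to check attribution.

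The consequence is confined to that summary. No data would be lost. The amount omitted would equal the share of treatment-emergent events judged unrelated, for which the protocol offers no figure, so no percentage should be attached to it. The correction is worth making because it settles which events the safety analysis counts.

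**What to change.** In the profile sentence of section 11.5, replace the restriction to drug-related events with *treatment-emergent adverse events, regardless of causality*. This matches the timing-based scope of 7.6 and the unrestricted endpoint of 11.2; the words on causality are an addition that makes the scope explicit. Present treatment-related events as an additional summary. Add incidence to the items evaluated in 11.5, as 7.6 and 11.2 already have it.

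State the treatment-emergent window. The collection limit in 8.2, 30 days after the last dose, can serve as its end; its start is for the sponsor to define, either in the protocol or in the statistical analysis plan.

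The cost is one revised sentence, a small addition to the list and one further table. The data are already collected, and neither the sample size nor clinical management changes.

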## 12. TRANSLATIONAL SUBSTUDY

### 12.1 Rationale

New therapeutic schemes in sarcomas are urgently needed, mainly for patients diagnosed with advanced or metastatic disease and for whom there is no possibility of effective treatment. An important and attractive therapeutic strategy is based on cell cycle regulation. In fact, the mitotic index, together with the percentage of necrosis and differentiation, is important for the prognosis of the histological grade of sarcomas and the *cinsarc* genetic signature includes 67 genes involved in mitosis and chromosome integrity.

Cell division is an extremely well-regulated process and includes DNA replication and chromosome segregation into two independent cells, containing the same information. The transition between the different phases of the cell cycle occurs in an orderly manner and is regulated by numerous cellular proteins. The best-known key regulatory proteins are the serine (Ser/S)-threonine (Thr/T) cyclin-dependent protein kinases (CDKs), which are activated at specific stages of the cell cycle. These protein kinases remain stable during the cell cycle, but in turn the levels of their activator proteins, the cyclins, vary in order to specifically activate a particular CDK. Briefly, all three types of cyclin D (D1, D2, and D3) interacting with CDK4 and CDK6 are important for entering G1, and for regulating progression from G1 to S phase, cyclin E associates with CDK2. Furthermore, during S phase, cyclin A binds to CDK2 and to enter M phase the same cyclin complexes with CDK1. Lastly, progression through mitosis is regulated by cyclin B in association with CDK1. However, not only cyclin-CDK complexes are involved in the control of cell cycle progression. Indeed, several other protein kinases (e.g., Aurora kinases) and many transcription factors (e.g. p53) are associated with the regulation of cell division by distinct mechanisms.

Protein kinases CDK4 and CDK6 are an important part of the cell cycle. These kinases phosphorylate the tumor suppressor protein Rb (pRb), in response to mitogenic signals and/or anti-proliferative factors, allowing cell cycle progression and entry into G1. Phosphorylation of Rb leads to its inactivation, which releases the transcription factor E2F, which is necessary for DNA synthesis and cell cycle progression. At this point, further phosphorylation of Rb is carried out by the cyclin E/CDK2 complex, which allows cell cycle progression through G1. Also important is the non-catalytic function of cyclin D-CDK4/6 during G1, which isolate the Cip/Kip CDK inhibitors, p21CIP1 and p27KIP1, thus facilitating CDK2 activation and cell cycle progression. In addition, CDK inhibitors (CKIs) such as p16INK4A and p27KIP1 develop an effective control of cell cycle progression, mainly by blocking the formation of cyclin-CDK complexes. The G1-S phase transition is made according to various requirements by entering the cell into G0 or, under some circumstances, into senescence (permanent cell cycle arrest), in cases where the conditions necessary for cell cycle progression are not met. On the other hand, a typical characteristic of cancer is the deregulation of the cell cycle. Several factors contribute to this, including the amplification or mutation of *CDK4* and *CDK6*, the amplification of cyclin-encoding genes, or the silencing of CKIs. In effect, it is likely that many oncogenic processes depend on high CDK4 and CDK6 activity. In sarcomas, CDK4 overexpression was detected in 92% of cases, in a series of 152 patients. In addition, high expression of proteins related to the Rb pathway is a common event in sarcomas. These results suggest that CDK4 and CDK6 activity is a therapeutic target to be considered.

Palbociclib (PD0332991) is a selective CDK4/6 inhibitor with a half maximal inhibitory concentration (IC50) between 10 to 15nM in in vitro studies. Palbociclib has been tested in several tumor types, including liposarcoma with CDK4 overexpression. In a phase II trial in patients with well-differentiated or dedifferentiated liposarcoma, treatment with palbociclib demonstrated a favorable progression free survival (PFS) (PFS at 12 weeks of 57% and a median PFS of 17.9 weeks), in addition to a complete response. In pre-clinical studies, the drug was shown to induce cell cycle arrest, senescence and cell death by apoptosis. Cell cycle arrest in G1 is independent on Rb phosphorylation, suppressing tumor growth in in vivo models. Nevertheless, mechanisms of resistance to CDK4 and CDK6 inhibitors have been described, such as loss of function of pRb or p16INK4A, or overexpression of cyclin D1 and CDK2. Palbociclib also plays an important role in inhibiting FoxM1 phosphorylation. CDK4/6 phosphorylates this transcription factor, stabilizing and activating FoxM1, which may lead to transcription of genes relevant to the G1-S transition, suppression of reactive oxygen species, protection of cells from senescence or transcription of pluripotency genes, which seem to play an important role in sarcomas (e.g. Sox2). Furthermore, FoxM1 is normally overexpressed in sarcomas, being negatively regulated by p53 and partially regulated by Rb and p21CIP1. Thus, FoxM1 overexpression in sarcomas may be related to the frequent absence of p53 function observed in these tumors. In fact, p53 mutations appear to be related to worse PFS and overall survival (OS) in patients with advanced STS, as recently described by our group. Our group also demonstrated that PD0332991 induces senescence in in vitro and in vivo models of sarcoma. The response to palbociclib correlates with *CDK4* messenger RNA

(mRNA) levels, with drug showing activity in lines with high *CDK4* levels and low activity in lines with low *CDK4* expression and high p16INK4A levels. Otherwise, palbociclib lowers tumor levels of CDK4.

Senescence is a process induced by different tumor suppressor proteins, such as p53, Rb, p21CIP1 and/or p16INK4A, in response to an oncogenic stimulus. Currently, senescence is considered to play an important role in preventing the development of malignant lesions from pre-malignant cells. The senescence process is usually associated with cell cycle arrest, but recently an important relationship with the anti-tumor immune response has been suggested. In effect, several studies suggest that the destruction of senescent cells by cells of the immune system is a key step in preventing tumor development. Immune cells involved in the immune surveillance of cancer include natural killer (NK) cells and macrophages.

Overall, palbociclib demonstrates activity in sarcomas, depending on CDK4 mRNA levels and in the context of p16INK4A low or normal levels. Other proteins important in palbociclib activity are p53, p21CIP1, p27KIP1, Rb, FoxM1 and cyclin D1. In addition, the CDK4 inhibitor induces senescence, which is connected with the immune response. Nonetheless, the fact that palbociclib also inhibits CDK6, which is present in the immune system, may negatively affect the response. Thus, the effect of palbociclib at the level of immune response modulation will be a secondary objective of this study.

